**Fig. 1 Fig1:**
[figure not shown]
ADIDAS trial design diagram. R, randomization; Qd, once daily; p.o., orally

### Participant Selection

Patients aged ≥18 years with elevated NT-proBNP or BNP levels on admission, ejection fraction (EF) <50%, and New York Heart Association (NYHA) class II, III, or IV are eligible for enrollment. Exclusion criteria include patients who received treatment with SGLT2i during the past 3 months, or previous intolerance of an SGLT2 inhibitor, or severe (eGFR<30 mL/min/1.73 m^2 by CKD-EPI), unstable, or rapidly progressing renal disease at the time of randomization, pregnant, and breastfeeding women (Table 1).

**Table 1 Tab1:** Inclusion and exclusion criteria of the ADIDAS trial

Inclusion criteria ▪ Male or female between the ages of 18 and 100 years ▪ Elevated NT-proBNP or BNP levels on admission ▪ Ejection fraction of 50% or less, and New York Heart Association (NYHA) class II, III, or IV symptoms	
Exclusion criteria ▪ Treatment with SGLT2i during the past 3 months of admission, or previous intolerance of an SGLT2 inhibitor ▪ Severe (eGFR<30 mL/min/1.73 m^2 by CKD-EPI), unstable, or rapidly progressing renal disease at the time of randomization ▪ Pregnant or breastfeeding female patients	

### Endpoints

The primary endpoint is a composite of hospital admissions for HF and all-cause death. Secondary endpoints include change in the Kansas City Cardiomyopathy Questionnaire (KCCQ) score and change in 6-min walk distance as well as hemoglobin level.

### Randomization

Eligible patients will be computer-randomized in a 1:1 ratio to receive either oral dapagliflozin 10 mg once daily or placebo 10 mg once daily for 12 months.

### Study Visit and Follow-up

The study visit and follow-up are shown in Fig. 1. After obtaining informed consent, during visit 1, we check the inclusion and exclusion criteria and collect baseline information (including clinical examination and laboratory measurements). Patients are randomized to dapagliflozin or placebo, and study drug is dispensed. Visit 2 takes place 6 months and visit 3 12 months. At each visit, the patient’s well-being and the occurrence of adverse events (including hospitalization and all-cause death) are assessed. Patents are requested to complete the Kansas City Cardiomyopathy Questionnaire (KCCQ) and 6-min walk test, and blood sample is drawn and analyzed to check hemoglobin level.

### Sample Size Determination and Statistical Analysis

The ADIDAS study is powered on the event rates of previous large-scale study [9]. The incidence of composite outcome worsening heart failure or death from cardiovascular causes is 16.3% in the dapagliflozin group versus 21.2% in the placebo group (hazard ratio, 0.74; 95% confidence interval (CI), 0.65 to 0.85; *P*<0.001), as shown by DAPA-HF trial [9]. Thus, we estimated that with a total of 1990 patients (995 per group) required to determine the anemia correction-related beneficial effects on outcomes, the power of the study would be 80% with a 2-sided type I error rate of 0.05. Assuming that 2% of patients would withdraw or be lost to follow-up, the final sample size is determined to be 2030 patients (1015 per group).

All analyses will be detailed prior to database lock and unblinding. Summary tabulations will be presented for categorical variables, in which the number and percentage of participants within each category will be shown. As for continuous variables, the mean, median, standard deviation, first and third quartiles, and minimum and maximum values will be presented. The level of significance to be used for tests will be 0.05.

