## Introduction

Heart failure (HF) is a severe clinical syndrome with high mortality and rehospitalization rate. The morbidity of HF is 1.5–2.0% in developed countries, and the rate is even more than 10% in people over 70 years old [1]. According to the epidemiological survey in 2003, the prevalence of heart failure in Chinese adults aged 35–74 was 0.9% [2]. It is estimated that its incidence will significantly rise within the near future.

In the 2017 ACC/AHA/HFSA Focused Update of the 2013 ACCF/AHA Guideline for the Management of Heart Failure, anemia, hypertension, and sleep-disordered breathing were listed as important comorbidities of heart failure [3], among which the incidence of anemia was 33.3% and the incidence of anemia was similar between patients with preserved left ventricular ejection fraction (LVEF) with HF (HFpEF) and reduced LVEF with HF (HFrEF) [4]. Moreover, anemia is independently associated with HF disease severity [3], poor functional capacity [5], hospitalizations, and mortality [4]. Clinical trials have demonstrated intravenous iron for the treatment of anemia improve exercise capacity and quality of life (QoL), but did not affect overall mortality [6, 7].

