Dapagliflozin is a sodium-glucose co-transporter 2 inhibitor (SGLT2i). Recent clinical trials showed that dapagliflozin use was associated with significantly reduced HF hospitalization [8], worsening heart failure or death from cardiovascular causes [9], and increased HF-related health status [10]. The Dapagliflozin Effect on Cardiovascular Events trial (DECLARE–TIMI 58) showed 27% reduction in HF hospitalization in the dapagliflozin group [8]. In the Dapagliflozin And Prevention of Adverse-Outcomes in Heart Failure trial (DAPA-HF), the incidence of composite outcome with worsening heart failure or death from cardiovascular causes was 16.3% in the dapagliflozin group versus 21.2% in the placebo group (hazard ratio, 0.74; 95% confidence interval (CI), 0.65 to 0.85; *P*<0.001) [9]. DEFINE-HF trial (Dapagliflozin Effects on Biomarkers, Symptoms and Functional Status in Patients with HF with Reduced Ejection Fraction) also demonstrated a meaningful improvement in HF-related health status or natriuretic peptides [10]. In another trial, treatment with dapagliflozin resulted in correction and prevention of anemia in patients with T2D, and hemoconcentration due to a diuretic effect (early phase) and increased erythropoiesis (late phase) might be the underlying mechanisms responsible for these effects [11]. Though clinical trials have demonstrated that SGLT2 inhibitors have impressive beneficial cardiovascular effects in HF patients both with and without diabetes, the actual mechanisms still remain elusive. Several potential theses have been proposed, including modulation on ventricular loading, cardiac energetics, sodium-hydrogen exchange, erythropoietin, progenitor cells, and CaMKII [12]. Studies also found that SGLT2 inhibitors could upregulate SIRT1, then activate hypoxia-inducible factor-2α (HIF-2α) and hypoxia-inducible factor-1α (HIF-1α), which can promote erythropoietin synthesis, and might contribute to erythropoiesis [13–16].

Anemia correction belongs to a feature of effective strategies on HF [17]; it remains unknown if anemia correction is a prerequisite of dapagliflozin-induced beneficial effects in HF patients. Thus, in this randomized clinical trial, we tested the hypothesis that anemia correction is a major determinant related to the beneficial effects of dapagliflozin in patients with heart failure.

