## Methods

### Study Design

The primary objective of the ADIDAS trial (ClinicalTrials.gov Identifier: NCT04707261) is to investigate the hemoglobin change and the association between hemoglobin change and readmissions due to heart failure and all-cause death in patients with heart failure treated with dapagliflozin or placebo.

The study will include up to 12 sites within the Hunan Province, China, and up to 2030 participants receiving guideline recommended standard therapy will be computer-randomized to either oral dapagliflozin 10 mg once daily group or placebo 10 mg once daily group; the therapy duration is 12 months. Patients will be followed at 6 months and 1 year after randomization (Fig. 1).

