Though clinical trials have evidenced that dapagliflozin have impressive beneficial cardiovascular effects in HF patients both with and without diabetes, the actual mechanisms still remain elusive. Numerous theories have been proposed to explain the beneficial effects of SGLT2 inhibitors; one of them is the increase of erythropoietin (EPO) levels. Study showed that SGLT2 inhibitors could raise the hematocrit [18], even in those without diabetes (as seen in DAPA-HF); it is speculated that these agents may promote erythropoiesis via enhanced EPO secretion by the kidney [19]. Mazer et al. [19] recently explored the impact of empagliflozin on EPO levels, red blood cell (RBC) morphology, and indices of iron stores in individuals with type 2 diabetes (T2D) and stable coronary artery disease (CAD). It was shown that EPO levels increased significantly after 1 month of empagliflozin treatment, and hematocrit increased after 6 months by 2.34% [95% CI 1.1, 3.57, *P*<0.001]. Studies also showed that SGLT2 inhibitors can stimulate SIRT1 and then activate hypoxia-inducible factor-2α (HIF-2α) and hypoxia-inducible factor-1α (HIF-1α), which can promote erythropoietin synthesis [13–16]. In another trial, dapagliflozin corrected anemia in 52% of patients with anemia at baseline (placebo: 26%), and the mechanism may be a combination of hemoconcentration due to a diuretic effect (early phase) and increased erythropoiesis (late phase) [11].

Anemia is a common comorbidity in patients with heart failure and associated with more severe symptoms and an adverse prognosis [3, 20]. Recent study suggested that dapagliflozin has beneficial effects on HF, and this effect might be related to the correction of anemia. A recent trial showed that intravenous iron replacement with ferric carboxymaltose reduced the risk of heart failure hospitalizations in patients with iron deficiency after an episode of acute heart failure [21]. SGLT2 inhibitors possess multiple mechanisms of improving HF syndrome, including correction of anemia; and our study aims to determine if elevation of hemoglobin is definitely linked with improved outcome in HF patients receiving placebo or dapagliflozin, if dapagliflozin use is associated with higher incidence of elevation of hemoglobin, and last but not least, if elevation of hemoglobin is accompanied by HF outcome improvement.

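### The stated 80% power belongs to the overall dapagliflozin-versus-placebo comparison; it is not established for the anemia-correction question to which the protocol attaches it

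*Protocol article*

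**What the plan says.** Four places in the protocol article bear on this.

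- **Sample Size Determination and Statistical Analysis** takes its rates from a previous large trial, "16.3% in the dapagliflozin group versus 21.2% in the placebo group" ("hazard ratio, 0.74; 95% confidence interval (CI), 0.65 to 0.85"). From these it concludes that 80% power at a two-sided 0.05 level is obtained "with a total of 1990 patients (995 per group) required to determine the anemia correction-related beneficial effects on outcomes". Adding 2% for withdrawal and loss gives 2030 (1015 per group).
- **Study Design** gives the primary objective: to "investigate the hemoglobin change and the association between hemoglobin change and readmissions due to heart failure and all-cause death".
- **Introduction** gives the hypothesis: that "anemia correction is a major determinant related to the beneficial effects of dapagliflozin in patients with heart failure".
- **Endpoints** says: "The primary endpoint is a composite of hospital admissions for HF and all-cause death". Hemoglobin level is listed among the secondary endpoints.

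**The concern.** The section names one question (benefit related to anemia correction) and computes the sample size for another (total benefit of the drug). The primary objective, the primary endpoint and the powered contrast do not line up, and the power sentence hides this by presenting an overall treatment comparison as a test about anemia.

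Two misreadings could follow. A positive result on the composite could be taken as confirming the anemia hypothesis, although it would show only that the drug works. A null result on hemoglobin or anemia could be taken as coming from an 80%-powered test, when no power for that test has been worked out.

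**Working it through.** **Inputs from the protocol article.** Event rates p1 = 0.163 and p2 = 0.212, difference 0.049; two-sided alpha 0.05 (z = 1.960); power 80% (z = 0.842); 1:1 allocation; 995 per group (all from the sample size and randomization sections). Anemia prevalence in heart failure of 33.3% (Introduction, as background). Anemia is not an entry criterion (Table 1).

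**Step 1: reproduce the stated figure.** Pooled two-proportion formula, no continuity correction:

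n = [1.960·√(2·p̄·q̄) + 0.842·√(p1q1 + p2q2)]² / (p2 − p1)²

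- p̄ = (0.163 + 0.212)/2 = 0.1875, so 2·p̄·q̄ = 0.3047 and its root is 0.5520.
- p1q1 + p2q2 = 0.1364 + 0.1671 = 0.3035, root 0.5509.
- n = (1.0819 + 0.4636)² / 0.002401 = 994.8, which rounds up to 995 per group, or 1990 in total.
- Power at 995 per group is 80.0%.
- 1990 × 1.02 = 2029.8, the stated 2030.

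A log-rank calculation at a hazard ratio of 0.74 does not give this figure: it needs 347 events, and 347/0.1875 is about 1851 patients. That hazard ratio is in any case also the overall treatment effect.

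**Step 2: what enters.** The two arm-level event rates, alpha and power reproduce 995 with nothing left over. No hemoglobin difference, prevalence, correction rate, hemoglobin-outcome association or mediated share is used. The 80% is the power of the arm comparison.

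**Step 3: illustrate power for the stated objective.** The effect size is not in the document, so a range is shown. Expected events are D = 995 × (0.163 + 0.212) = 373. For a continuous covariate in a proportional hazards model, without adjustment, power = Φ(√D·|ln HR| − 1.960), with HR per standard deviation of hemoglobin change and √373 = 19.31.

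| HR per SD (assumed) | √D·abs(ln HR) | Power |
|---|---|---|
| 0.95 | 0.99 | 17% |
| 0.90 | 2.03 | 53% |
| 0.85 | 3.14 | 88% |
| 0.80 | 4.31 | 99% |

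80% is reached at HR = exp(−2.80/19.31), about 0.86 per SD. This uses every event. The first post-baseline hemoglobin is taken at 6 months; if only half the events (about 187, an assumption) fall after it, 80% power needs about 0.81 per SD, and power at 0.90 is about 30%.

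**Step 4: if the question is limited to anemic patients.** Assume that 33.3% applies here and that event rates are the same: 995 × 0.333 is about 331 per group. Power = Φ[(0.049·√331.3 − 1.0819)/0.5509] = Φ(−0.345), about 37%. To have 995 anemic patients per group, 1990/0.333, or about 5,976, would have to be enrolled.

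**The case against.** **The basis of the sample size is disclosed.** The section opens by saying that the study is powered on a previous trial's event rates, the arithmetic reproduces, and the composite by arm has the stated power under those rates. This stands: neither the number nor the primary-endpoint power is in error. What is wrong is the hypothesis to which the power is attached.

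**The analysis can be left to the analysis plan.** The method for the hemoglobin analysis can. But the article states what the sample size is for, and a later document cannot turn 995 per group into an anemia calculation.

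**Power for the objective may be ample.** A reader might infer that the trial falls short of 80% for its primary objective. The documents do not support that. The objective has two parts. For hemoglobin change by arm, 80% power needs a difference of only 2.80 × √(2/995), about 0.13 SD. For the association with outcome, Step 3 shows that power passes 80% at about HR 0.86 per SD or stronger. The shortfall is in justification, not in demonstrated power.

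**Subgroup and mediation figures go beyond the stated design.** A reader might also infer that anemia correction cannot account for the assumed benefit: 33.3% × (52% − 26%) = 8.7% of an arm is net corrected, and 8.7% × 21.2% is only 1.8 of the 4.9 points. This too is not supported as a fact about this trial. The correction rates come from patients with type 2 diabetes, and the prevalence is background. If anemic patients had twice the 21.2% risk, the ceiling would be 3.7 points. The sum also ignores any benefit of a hemoglobin rise in patients who cross no anemia threshold. Likewise, no test confined to anemic patients and no treatment-by-anemia interaction is planned in the article, so the 37% in Step 4 is conditional on a narrower question than the stated objective.

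**Conclusion.** The concern holds as a misattributed power statement. The 995 per group, and with it the 80%, belongs to the randomized dapagliflozin-versus-placebo comparison of the composite. It is not established for hemoglobin change and its association with outcome, nor for the hypothesis that anemia correction is a major determinant of benefit.

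The true power for that objective cannot be given as one figure. It runs from about 17% to 88% for hazard ratios of 0.95 to 0.85 per SD with about 373 events, and is about 37% for the arm contrast among anemic patients only. These figures assume the cited event rates apply to this trial's composite (the cited outcome was worsening heart failure or cardiovascular death, so the definitions differ), an unadjusted analysis using all events, and, for the last figure, 33.3% prevalence with equal event rates. The misattribution itself rests on none of these assumptions; it follows from the stated inputs alone.

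**What to change.** 1. Reword the sample size sentence so that 80% power at 995 per group refers only to the randomized comparison of dapagliflozin with placebo on the composite.
2. Name that comparison as the primary analysis, matching the primary endpoint.
3. For the hemoglobin/anemia objective, do one of two things: state an effect size and the resulting power or precision, using hemoglobin change as a continuous variable so that non-anemic patients contribute; or state plainly that the objective is not formally powered.

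The objective need not be demoted to secondary. That is one option, but it would change the trial's declared purpose; the sponsor may keep it in place provided its power is derived separately or disclaimed.

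Cost: wording in the protocol and analysis plan, and no extra patients. The article says enrollment had not started, so the change could be made before any data exist. The downside is that the protocol can no longer claim 80% power for the anemia question.

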### Study Administration and Management

The trial is registered as ClinicalTrails.gov Identifier: NCT04707261. The local Institutional Review Board or Ethics Committee at each participating institution must approve the study, and all patients must provide written informed consent prior to enrollment. Funding is provided by the Department of Cardiology, The Xiangtan Central Hospital. The Xiangtan Central Hospital maintains the complete study database and will perform all key analyses. An independent data monitoring committee (DMC), composed of three physicians from the fields of cardiology and interventional cardiology and one biostatistician, reviews aggregate and individual patient data related to safety, data integrity, and overall conduct of the trial, on a periodic basis. The DMC may make recommendations to the steering committee and study sponsor as a result of its monitoring activities. The study has not started enrollment, and we plan to complete the enrollment of all subjects between February 2021 and January 2024, and the follow-up will last 1 year.

## Discussion

The ADIDAS trial is an investigator-initiated, interventional, prospective, double-blind, multicenter study involving patients with HF. All eligible participants receiving guideline recommended standard therapy will be computer-randomized to either oral dapagliflozin 10 mg once daily or placebo 10 mg once daily for 12 months.

The study is designed based on previous related clinical trials. The DECLARE–TIMI 58 trial [8] was a placebo-controlled, phase 3 trial in patients with type 2 diabetes who had or were at risk for atherosclerotic cardiovascular disease to receive either dapagliflozin or placebo; the result showed that dapagliflozin resulted in a lower rate of cardiovascular death or hospitalization for heart failure (4.9% vs. 5.8%; hazard ratio, 0.83; 95% CI, 0.73 to 0.95; *P*=0.005), which reflected a lower rate of hospitalization for heart failure (hazard ratio, 0.73; 95% CI, 0.61 to 0.88). The DAPA-HF study [9] demonstrated that dapagliflozin treatment lowed the risk of worsening heart failure or death from cardiovascular causes (16.3%) versus placebo treatment (21.2%) in HF patients, regardless of the presence or absence of type 2 diabetes. While DEFINE-HF trial demonstrated, there was a meaningful improvement in Kansas City Cardiomyopathy Questionnaire overall summary score or NT-proBNP, 61.5% of dapagliflozin-treated patients versus 50.4% with placebo (adjusted OR 1.8, 95% CI 1.03–3.06, nominal *P*=0.039) [10].

Though clinical trials have evidenced that dapagliflozin have impressive beneficial cardiovascular effects in HF patients both with and without diabetes, the actual mechanisms still remain elusive. Numerous theories have been proposed to explain the beneficial effects of SGLT2 inhibitors; one of them is the increase of erythropoietin (EPO) levels. Study showed that SGLT2 inhibitors could raise the hematocrit [18], even in those without diabetes (as seen in DAPA-HF); it is speculated that these agents may promote erythropoiesis via enhanced EPO secretion by the kidney [19]. Mazer et al. [19] recently explored the impact of empagliflozin on EPO levels, red blood cell (RBC) morphology, and indices of iron stores in individuals with type 2 diabetes (T2D) and stable coronary artery disease (CAD). It was shown that EPO levels increased significantly after 1 month of empagliflozin treatment, and hematocrit increased after 6 months by 2.34% [95% CI 1.1, 3.57, *P*<0.001]. Studies also showed that SGLT2 inhibitors can stimulate SIRT1 and then activate hypoxia-inducible factor-2α (HIF-2α) and hypoxia-inducible factor-1α (HIF-1α), which can promote erythropoietin synthesis [13–16]. In another trial, dapagliflozin corrected anemia in 52% of patients with anemia at baseline (placebo: 26%), and the mechanism may be a combination of hemoconcentration due to a diuretic effect (early phase) and increased erythropoiesis (late phase) [11].

Anemia is a common comorbidity in patients with heart failure and associated with more severe symptoms and an adverse prognosis [3, 20]. Recent study suggested that dapagliflozin has beneficial effects on HF, and this effect might be related to the correction of anemia. A recent trial showed that intravenous iron replacement with ferric carboxymaltose reduced the risk of heart failure hospitalizations in patients with iron deficiency after an episode of acute heart failure [21]. SGLT2 inhibitors possess multiple mechanisms of improving HF syndrome, including correction of anemia; and our study aims to determine if elevation of hemoglobin is definitely linked with improved outcome in HF patients receiving placebo or dapagliflozin, if dapagliflozin use is associated with higher incidence of elevation of hemoglobin, and last but not least, if elevation of hemoglobin is accompanied by HF outcome improvement.

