**Purpose:**

This investigator-initiated, interventional, prospective, double-blind, multicenter study is designed to investigate whether anemia correction is one of the prerequisites and determinants related to the beneficial effects of dapagliflozin in HF patients.

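### The prerequisite/determinant hypothesis is to be answered by a non-randomized association between hemoglobin change and outcome, which cannot carry a causal conclusion

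*Protocol article*

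**What the plan says.** The causal question appears twice in the protocol article. The Purpose in the Abstract is to investigate "whether anemia correction is one of the prerequisites and determinants related to the beneficial effects of dapagliflozin in HF patients". The Introduction states: "we tested the hypothesis that anemia correction is a major determinant related to the beneficial effects of dapagliflozin in patients with heart failure".

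The comparison meant to answer it is associational. Under Study Design, the primary objective is to "investigate the hemoglobin change and the association between hemoglobin change and readmissions due to heart failure and all-cause death" in patients on either treatment. The Discussion sets three aims: "if elevation of hemoglobin is definitely linked with improved outcome in HF patients receiving placebo or dapagliflozin", whether dapagliflozin raises hemoglobin more often, and whether a rise goes along with better HF outcome.

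Participant Selection contains no hemoglobin criterion, so anemic and non-anemic patients both enter. Study Visit and Follow-up provides for laboratory measurements at visit 1 and hemoglobin at each visit (6 and 12 months thereafter). Baseline hemoglobin will therefore be known. The article names no treatment effect by baseline hemoglobin or anemia.

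**The concern.** Of the three aims, only the effect of the drug on hemoglobin compares randomized arms. The other two relate a post-randomization variable to outcome. All three can be positive when hemoglobin plays no causal part: the drug raises hemoglobin and separately lowers events, while less ill patients both raise their hemoglobin and have fewer events.

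The Discussion itself supplies such paths. It says that SGLT2 inhibitors act through several mechanisms, that part of the hemoglobin effect may be hemoconcentration, that anemia goes with worse symptoms and prognosis, and that intravenous iron reduced HF hospitalizations. In addition, hemoglobin is rechecked only at 6 and 12 months, so some events precede the measured change, and patients who die before 6 months have no follow-up value.

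At stake is the reading of the main mechanistic result: an observed link could be reported as confirming a prerequisite or determinant.

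**Working it through.** **1. The plan's own figure.** Inputs (Sample Size Determination and Statistical Analysis): p1 = 0.163, p2 = 0.212, two-sided alpha 0.05, power 80%. With p̄ = 0.1875,

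n per group = [1.960·√(2p̄(1−p̄)) + 0.8416·√(p1(1−p1) + p2(1−p2))]² / (p2−p1)² = (1.0819 + 0.4636)² / 0.049² ≈ 994.9, rounded up to 995.

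This matches the stated 995 per group (1990 in total). It is a plain drug-versus-placebo comparison. No input concerns hemoglobin, although the section presents the number as serving benefit related to anemia correction.

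**2. Can a link appear with no causal role for hemoglobin?**

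*Treatment alone, arms pooled.* Borrow the correction rates of 52% and 26% quoted in the Discussion. They come from patients anemic at baseline in a trial that the Introduction describes as in type 2 diabetes, so their use here is an assumption.
- Corrected: share on drug 0.52/0.78 = 0.667; risk 0.667×0.163 + 0.333×0.212 = 17.9%.
- Not corrected: share on drug 0.48/1.22 = 0.393; risk 0.393×0.163 + 0.607×0.212 = 19.3%.
- Risk ratio 0.93. With 995×0.78 = 776 and 995×1.22 = 1214 patients, z = 0.0134 / √(0.1875×0.8125×(1/776 + 1/1214)) ≈ 0.75. Within each arm this effect vanishes.

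*Prognosis.* A simulation of 2,000,000 patients used the same arm-specific rates, no effect of hemoglobin on outcome, and an unmeasured severity factor that lowers the chance of a rise and raises the chance of an event. The factor's strength is assumed.

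| Log-odds per SD | Within-arm odds ratio | Pooled odds ratio |
|---|---|---|
| 0 | about 1.0 | 0.92 |
| 0.5 | about 0.80 | 0.74 |
| 1.0 | about 0.47 | 0.45 |

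Analysis within arms removes the part due to treatment but not the part due to prognosis.

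**3. What the randomized comparison by baseline anemia can show.** Assumptions: 33.3% anemic (the HF figure in the Introduction) and the same event rate in both strata. Expected events: (0.163 + 0.212)×995 = 373, split 124 anemic and 249 non-anemic.

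SE of the log ratio of hazard ratios = √(4/124 + 4/249) = 0.220. Smallest ratio detectable at 80% power: exp(−2.80×0.220) = 0.54.

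Power = Φ(|ln ratio|/0.220 − 1.96):

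| HR anemic vs non-anemic | Power |
|---|---|
| 0.41 vs 1.0 (strict prerequisite, overall 0.74) | 98% |
| 0.50 vs 0.90 | 76% |
| 0.60 vs 1.0 | 64% |
| 0.60 vs 0.82 | 30% |
| 0.74 vs 1.0 | 28% |

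The 0.41 is 0.74^(1/0.333). For the strict pattern, power is above 99% at 20% anemia and 83% at 50%.

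Within non-anemic patients alone, power for HR 0.74 is Φ(√(249/4)×0.301 − 1.96) = 66%. On the risk scale, 1015×0.667 = 677 non-anemic patients per arm give a 95% half-width of 1.96×√((0.1364 + 0.1671)/677) = 4.2 points, against a planned difference of 4.9 points.

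These powers depend on each stratum's share of events. If anemic patients carried half the events because of worse prognosis, the 50% figures would apply: 83% for the strict pattern, and 54% within non-anemic patients.

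**The case against.** The strongest reply has three parts.

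*The operative text is already associational.* The primary objective, the Abstract's Conclusions and the Discussion speak of association or linkage, and an association can be estimated as written. This stands in part. A reader might infer that the trial cannot answer its question, or that it is committed to a causal conclusion. The documents show neither. What remains is that the purpose and hypothesis ask for more than the stated comparison can give, and that the Discussion's qualifier (definitely) strengthens the link further.

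*Analysis detail is deferred.* The article says that analyses will be detailed before database lock, and it is condensed. So a missing subgroup analysis, covariate list or stratification factor is no fault, and none is claimed. The fault is the stated pairing of a causal hypothesis with a non-randomized comparison, which an analysis plan would inherit.

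*Baseline anemia is not a direct test of the mechanism.* This stands. Hemoglobin can rise in non-anemic patients too, so benefit among them contradicts only the strict prerequisite reading. It says nothing on mediation or on *determinant*.

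It is also tempting to read the pooled risk ratio of 0.93 as proof of a false link. It is too small for that (z about 0.75), disappears within arms and rests on borrowed rates. The argument rests on confounding by prognosis, whose size here is unknown.

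**Conclusion.** The concern holds as a mismatch in stated text: a causal hypothesis is paired with an association that randomization does not protect. The randomized comparison of dapagliflozin with placebo on the composite is unaffected.

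The size of the possible bias cannot be derived from the documents. The simulated odds ratios show only that a moderate or strong link can arise with no causal role for hemoglobin. A randomized check of the strict prerequisite reading is available from data already collected, but it is well powered only for a near all-or-none pattern. That rests on 33.3% anemia, event rates equal in both strata and the planned event rates being met.

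**What to change.** 1. Pre-specify the randomized treatment effect on the composite by baseline anemia, with a treatment-by-baseline-hemoglobin interaction, as the test of the strict prerequisite reading. Benefit in patients without baseline anemia contradicts that reading. State in advance that a non-significant result in those patients is not support for it.
2. In any hemoglobin-outcome model, include treatment and baseline hemoglobin. Report it as exploratory mediation, with a sensitivity analysis for unmeasured confounding of hemoglobin and outcome. The interaction in item 1 does not replace this for the *determinant* question.
3. In the conclusions, replace *prerequisite*, *determinant* and *definitely linked* with *associated with*, unless items 1 and 2 support more.

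The cost is wording in the protocol and the analysis plan; baseline hemoglobin is already measured. Stratifying randomization by anemia is optional, since the subgroup comparison is valid without it. The downside is an imprecise interaction estimate, which should be reported with its confidence interval and described as such.
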